#### Outcomes and assessments

For Component 1, participants will be asked to complete assessments at three time points. Baseline (or Time 1) assessments will be administered prior to the start of P-CFT (up to 4 weeks prior to the first treatment session). Post-intervention (or Time 2) assessments will be undertaken after the intervention phase (which will be up to 4 weeks post-intervention), with a final follow-up assessment at six months after baseline (referred to as Time 3).

Participants will be asked to complete a socio-demographic questionnaire which will provide information on the following: their NHS trust where they received P-CFT, current age, ethnicity, current relationship status, employment status, financial and socioeconomic situation, highest level of education, primary mental health diagnosis and whether or not they have received previous psychological treatment. The questionnaire will also collect data on age of youngest child and genders and ages of other children. At post-intervention, participants will be asked to provide the number of how many sessions of P-CFT they attended, as part of the online questionnaires.

#### Primary feasibility and acceptability outcomes

Data will be collected to indicate levels of feasibility and acceptability. Retention rates of participants in the study will be examined, which will be the number of consented participants who remain in Component 1 at post-intervention and follow-up. The number of eligible patients who consent to participate in the study as well as the number of patients who decline to participate will also be recorded to assess the feasibility of recruitment strategies. To assess the feasibility of the P-CFT intervention, the attendance of the group sessions will be collected. In addition, the rate of completion of the self-reported outcome measures across each time point will be used to signify their feasibility and acceptability.

#### Secondary clinical outcomes

A set of validated outcome measures will also be administered to assess the feasibility and acceptability of data collection in relation to compassion-based outcomes and mood. Details of the validated outcome measures are listed below and displayed in **Table 2**. Compassion will be examined using the *Fear of Compassion* (FCS) - *Fear of self-compassion subscale* (*FCS-SC*) (32) and the *Sussex-Oxford Compassion for Self scale (SOCS)* (33). This study will be able to assess if one compassion-based measure is more acceptable to participants. General presentation of mood will be measured with the *Clinical Outcomes in Routine Evaluation* (CORE-10) (35) and the *Depression, Anxiety and Stress Scale* (DASS-21) (36). The CORE-10 is a routinely collected measure in perinatal services (56). In addition to the DASS-21 use in other CFT studies, this measure was selected due to the associated improvements of anxiety and depression following CFT (18). Furthermore, the *Short Warwick-Edinburgh Mental Wellbeing Scale* (SWEMWBS) (37) will be administered to measure levels of wellbeing. Assessment of postpartum bonding will be evaluated using the *Postpartum Bonding Questionnaire* (PBQ) (34), which is also routinely collected in perinatal services (56). In addition, measures were selected based on their psychometric properties (see **Table 2** for details and the order of administration) and in consultation with the study’s PPIE group and the site group facilitators. As the CORE-10 and PBQ are measures that are already routinely collected by the perinatal services, participants are not required to complete these two measures as part of the study’s online questionnaire. In the event where consented participants do not complete the CORE-10 and PBQ during the study’s baseline assessment, the research team will request the scores from the group facilitators.

**Table 2 T2:** Overview of the study’s outcome measures and psychometric properties in order of delivery.

Outcome measure properties									Psychometric properties	
Order of administration	Outcome measure	Aim	Item numbers	Scoring range	Score interpretation	Scale type	Response choices		Internal reliability (Cronbach’s alpha)	Test retest reliability
*1*	*Fear of Compassion* (FCS): *Fear of self-compassion subscale (*FCS-SC) (32)	Measuring kindness and compassion towards oneself	15 in total	0-21	Higher scores are indicative of increased fear of self-compassion	4-point Likert scale	‘Don’t agree at all’ to ‘Completely agree’		.92 (32)	Not available
*2*	*Sussex-Oxford Compassion for Self scale* (SOCS) (33)	Assesses how an individual relates to themselves	9 in total	0-21	Higher score reflects higher level of self-compassion	4-point Likert scale	‘Not at all’ to ‘Nearly every day’		.93 (45)	ICC:.73–78 (46)
*3*	*Postpartum Bonding Questionnaire* (PBQ) (34)	Measures difficulties in the parent-infant bond	25 in total Subscales: *12 for Impaired bonding (PBQ-IB)* *7 for Rejection and anger (PBQ-RA)* *4 for Infant-focused anxiety (PBQ-IFA)* *2 for Incipient abuse (PBQ-IA)*	0–125 total *PBQ-IB: 0-60* PBQ-RA: *0-35* *PBQ-IFA: 0–20 PBQ-IA:0-10*	Higher scores are indicative of increased bonding difficulties	6-point Likert scale	‘Always’ to ‘Never’		.78-.79 (47)	r = .77-.95 (48)
*4*	*Clinical Outcomes in Routine Evaluation-10* (CORE-10) (35)*	Assessing levels of psychological distress	10 in total	0-4	Higher scores are indicative of increased distress	5-point Likert scale	‘Not at all like me’ to ‘Extremely like me’		.82-.84 (49, 50)	r = .76 (51)
*5*	*Depression, Anxiety, and Stress Scale-21* (DASS-21) (36)	Measuring levels of depression, anxiety, and stress	0–21 in total. 7 for each subscale: *Depression (DASS-D)* *Anxiety 9DASS-A)* *Stress (DASS-S)*	0–21 for each subscale**	Higher scores reflect level of severity	4-point Likert scale	‘Never to ‘Almost always’		.76 -.93 (52)	ICC = .82 -.86 (53)
*6*	*Short Warwick-Edinburgh Mental Wellbeing Scale* (SWEMWBS) (37)	Assessment of well-being	7 in total	7-35	Higher scores are indicative of better well-being	5-point Likert scale	‘None of the time’ to ‘All of the time’		.88-.93 (54)	r = .86 (55)

* Measures that were routinely collected by the service.

**Summed score of each subscale is required to be multiplied by 2.

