Since Millard and Wittkowski’s (21) review, another two evaluations of P-CFT groups in P-CMHTs were published: in both evaluations, service users experienced more moderate to severe PMH difficulties (27, 28). Service users presenting with a wide range of mental health difficulties were included, such as anxiety, posttraumatic stress disorder (PTSD), complex PTSD or birth trauma, obsessive compulsive disorder (OCD), personality disorders, and eating disorders. Both evaluations reported significant improvements across compassion-based outcomes, mood, and postpartum bonding, but no control groups were implemented. Although these two evaluations provided an insight into the potential benefits of P-CFT, the data were extracted retrospectively from self-reported outcomes in electronic health records. It is unclear from these evaluations if a further exploration into P-CFT is feasible in an NHS perinatal service. Given the limitations of the above-mentioned studies, a study using a stronger methodological rigour is required to explore the potential benefits of P-CFT. However, prior to a large-scale efficacy study, further exploratory studies are warranted (29). This multisite study aims to explore the feasibility and acceptability of the P-CFT groups based on Cree (10, 11) and the study design in perinatal mothers and birthing parents through three components. More specifically, the objectives are as follows:

to explore the feasibility of the study design through recruitment and retention rates and quality of data collection (Component 1, Component 2),to determine the suitability of the outcomes and their respective measures (Component 1),to assess the acceptability of the intervention through a qualitative process evaluation to identify factors associated with engagement and adherence to P-CFT (Component 3),to conduct an exploration of P-CFT has on compassion-based outcomes (i.e., self-compassion, self-criticism), psychological well-being and parent-infant interactions (Component 1, Component 2, Component 3).

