In particular, the feasibility of the online implementation of the MACI, the parent-infant video interactions can be evaluated. In previous studies, the data collection of this tool has primarily been conducted in-person with the participants (60). However, this method was not feasible for this study due to the locations of the recruitment sites. As recruitment is being delivered online, some novel aspects require evaluation for feasibility. Srikar et al. (59) reported that an online/remote version of the MACI-Infant measure was feasible to use in mothers with infants at elevated likelihood of autism. Nevertheless, it is unclear if an online/remote delivery of the MACI-Infant is feasible among mothers with perinatal mental health difficulties. From a practical perspective, this current study will look at aspects such as whether or not the interaction can be sufficiently set up remotely by participants, whether the self-recordings can be correctly recorded and sent to the researchers through their home devices and the suitability of recording through teleconferencing software, and generally, whether this method is acceptable among the group of mothers and birthing parents. As Component 2 is an optional aspect of the study, the recruitment rate will be able to indicate the willingness of participants to take part in a caregiver-infant interaction study. A meta-synthesis of parental experiences of video feedback parenting interventions highlighted that participating in recorded video interactions can often elicit feelings of self-doubt and anxiety (71). The implementation of remote data collection may help to mitigate this potential issue.

It is important to identify the appropriate outcome measures for perinatal mothers and birthing parents experiencing mental health difficulties. Some of the outcome measures and/or their specific items may elicit distress in participants. By allowing the participants to skip items that they may not be comfortable in answering, the study can determine which specific items or questionnaires are acceptable in this population.

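### With one fixed questionnaire order, raw completion rates favour the earlier measures, which weakens the acceptability comparison, mainly for DASS-21 and SWEMWBS

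*Protocol article*

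**What the plan says.** Four parts of the protocol article bear on this.

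- **Order.** The title of Table 2 says it gives the "outcome measures and psychometric properties in order of delivery". A column numbers the measures 1 to 6: FCS-SC, SOCS, PBQ, CORE-10, DASS-21, SWEMWBS. The text of *Secondary clinical outcomes* also sends the reader to that table "for details and the order of administration". The article does not say in words that every participant gets this order, but it states no other and mentions no rotation or counterbalancing.
- **Metric.** Under *Primary feasibility and acceptability outcomes*, "the rate of completion of the self-reported outcome measures across each time point will be used to signify their feasibility and acceptability".
- **Comparative claims.** *Secondary clinical outcomes* says of FCS-SC and SOCS: "This study will be able to assess if one compassion-based measure is more acceptable to participants". The *Discussion* adds that, because participants may skip items, "the study can determine which specific items or questionnaires are acceptable in this population". Both serve the second objective in the *Introduction*, on the suitability of the Component 1 measures.
- **Collection route.** PBQ and CORE-10 are collected routinely by the services, so "participants are not required to complete these two measures as part of the study’s online questionnaire". Baseline scores not given online are requested from the group facilitators.

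**The concern.** Each measure always occupies the same place in the list, so a low completion rate has two possible explanations: participants disliked the instrument, or they had stopped or tired before reaching it. A raw completion rate does not distinguish them. An item left blank after someone has stopped also looks the same as an item skipped from discomfort, unless break-off is identified first.

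The bias has one direction: it favours measures near the top. It does not shrink with more recruits. At stake is what the study can say about which instruments suit this population. SWEMWBS and DASS-21, at the end of the list, could look less acceptable than they are. PBQ and CORE-10 have a further problem, because their completion also depends on the route by which scores were obtained.

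**Working it through.** The plan states no figure to reproduce, because it gives no break-off rate and no expected completion rate. The calculation below shows how large a gap position alone could create.

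**Inputs from the documents.** Order of measures and item counts 15, 9, 25, 10, 21 and 7 (Table 2); planned baseline sample of 32 (*Sample size consideration*, Component 1).

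**Assumption.** All measures are equally acceptable, and a participant stops at each questionnaire with the same probability h. Since h is not in the documents, 2%, 5% and 10% are shown.

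**Formula.** Completion at position k = (1 − h)^k. False gap between positions 1 and k = (1 − h) − (1 − h)^k.

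| Completion | h = 2% | h = 5% | h = 10% |
|---|---|---|---|
| FCS-SC, position 1 | 98% | 95% | 90% |
| SOCS, position 2 | 96% | 90% | 81% |
| DASS-21, position 5 | 90% | 77% | 59% |
| SWEMWBS, position 6 | 89% | 74% | 53% |

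| False gap to FCS-SC (points) | h = 2% | h = 5% | h = 10% |
|---|---|---|---|
| SOCS | 2 | 5 | 9 |
| DASS-21 | 8 | 18 | 31 |
| SWEMWBS | 9 | 21 | 37 |
| SWEMWBS if PBQ and CORE-10 are not answered online (position 4) | 6 | 14 | 24 |

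In participants out of 32, the SOCS gap is 0.6, 1.5 or 2.9. The SWEMWBS gap is 3.0, 6.9 or 11.8, or 1.8, 4.3 or 7.8 when it is fourth.

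**Sensitivity to the model.** Let the chance of stopping be q per item instead, so that completion is (1 − q)^(cumulative items). The cumulative counts are 15 for FCS-SC, 24 for SOCS and 87 for SWEMWBS (52 without the 35 items of PBQ and CORE-10). With q = 0.1%, 0.25% or 0.5%, again assumed:

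- FCS-SC 98.5%, 96.3% or 92.8%; SOCS 97.6%, 94.2% or 88.7%; gap 1, 2 or 4 points.
- SWEMWBS 91.7%, 80.4% or 64.7%; gap to FCS-SC 7, 16 or 28 points, or 4, 9 or 16 points with 52 items.

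Both models give the same pattern: a small gap for the adjacent compassion pair and a larger one for the last measure.

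**Effect of the remedies.** Among those who reach a measure, completion under the per-questionnaire model is (1 − h)^k ÷ (1 − h)^(k−1) = 1 − h at every position, so the false gap is 0. If half of participants meet FCS-SC first and half SOCS first, each scale averages [(1 − h) + (1 − h)²] ÷ 2 and the gap is again 0. Under the per-item model, alternating leaves SOCS 0.3 to 1.4 points ahead, because it has 9 items against 15. That is a length effect, and length can fairly be counted as part of acceptability.

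**The case against.** The strongest replies, and what stands of each:

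- **The named comparison is the least affected.** FCS-SC and SOCS are adjacent. One participant in 32 is 3.1 points, so at h = 2% the false gap is under one person. This stands, and it is why the weight of the point falls on DASS-21 and SWEMWBS. A reader might infer that the study would favour FCS-SC over SOCS. The documents do not support that: even the direction depends on the denominator. Under the per-item model at q = 0.25%, completion among those who reach each scale is 96.3% for FCS-SC (0.9975^15) and 97.8% for SOCS (0.9975^9).
- **The break-off part can be separated in analysis.** A reader might conclude that no analysis can disentangle position from acceptability, or that the second objective cannot be met. Neither follows. Conditioning on having reached a measure removes break-off without any change of order, and selective skipping followed by continued answering is a different signal. What conditioning does not remove is fatigue among those who continue, or carry-over from one compassion scale to the next. The size of both is unknown.
- **No decision rule is stated.** A reader might infer that a measure would be dropped on its completion rate and the choice carried into a definitive trial. No section says so. Effect sizes and reliable change are also to be reported for the measures (*Data analysis of secondary outcomes*).
- **Denominators may be set out in a fuller document.** That is possible, and the analysis part of the fix may only need confirming. The order, however, is a feature of data collection that the article itself states, alongside the comparative claims. The interview topics listed in *Interview topic guide development* cover referral, group content and delivery, and benefits, not the questionnaires.
- **A constant order has merit, and the change comes late.** It keeps context effects alike across people for the pre-post summaries. Recruitment began in November 2023 and ends around March 2026, so alternating the order reaches only an unknown remainder. Both stand, and the fix is ordered accordingly.

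**Conclusion.** The point holds as a limit on what raw completion rates can show. With a single stated order and no stated adjustment for position, lower completion of a later measure cannot be read as lower acceptability.

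The size rests wholly on assumed break-off. At 2% to 10% per questionnaire it is 2 to 9 points for the compassion pair and 9 to 37 points for FCS-SC against SWEMWBS, or 6 to 24 if PBQ and CORE-10 are not answered online. Nothing in the documents shows which part of that range applies; if break-off proves negligible, so does this part of the bias.

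What is weakened is the comparative acceptability part of the second objective, chiefly for DASS-21 and SWEMWBS. The rest of that objective is unaffected.

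**What to change.** 1. **For all participants, including those already recruited:** report completion and item-skip rates for each measure among those who reached it, and tabulate the point of break-off separately. This costs one extra table.
2. **Treat PBQ and CORE-10 separately:** they are not required online and their baseline scores can come from facilitators, so report online completion and facilitator-supplied scores apart.
3. **For any remaining recruits:** alternate at least FCS-SC and SOCS in Qualtrics, which already hosts the forms. Record the order, hold it constant within each participant across Times 1 to 3, and amend the order shown in Table 2. The cost is a platform setting and a line of amendment, with slight order-related variation in scores between participants.
4. **Where order did not vary:** qualify the comparative claims in *Secondary clinical outcomes* and the *Discussion*, saying that fatigue and carry-over cannot be separated from acceptability.

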**Figure 1 f1:**
[figure not shown]
CONSORT diagram showing study design.

**Table 1 T1:** Overview of recruitment and assessment timeframes.

Study Elements			Study period			
Component	Time point	Enrolment	Time 1 (Baseline)	Intervention (Week 1 to 10/12)	Time 2 (Post-intervention)	Time 3 (Follow-up)
Enrolment						
1, 2, 3	Eligibility screening	X				
1, 2, 3	Consent to contact	X				
1, 3	Informed consent		X		X	
Intervention						
1, 2, 3	P-CFT			X		
Assessments						
1	Demographic Questionnaire		X			
1	Fear of Self-Compassion Scale (FOSC) (32)		X		X	X
1	Sussex-Oxford Compassion for Self (SOCS) (33)		X		X	X
1	Postpartum Bonding Questionnaire (PBQ) (34)		X		X	X
1	Clinical Outcomes in Routine Evaluation (CORE-10) (35)		X		X	X
1	Depression, Anxiety, and Stress Scale-21 (DASS-21) (36)		X		X	X
1	The Short Warwick-Edinburgh Mental Well-Being Scale (SWEMWBS) (37)		X		X	X
2	Parent-infant video interaction		X		X	
3	Semi-structured interviews with up to 12–14 participants				X	

As part of Patient and Public Involvement and Engagement (PPIE), two groups from two of the study research sites were consulted on the project and design of the research. Points made by the PPIE groups were considered and incorporated into the study protocol and participant documents. Throughout the study, the PPIE group will be consulted as required, such as on dissemination processes.

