#### Participant inclusion/exclusion criteria

Mothers and birthing parents are first referred to and assessed by the P-CMHT to determine their suitability for the service. If they meet the service criteria, they can be referred to the P-CFT group. Once enrolled to receive P-CFT and consent-to-contact is provided, the research team will assess a service user’s eligibility against the study criteria. To participate in the study, it is required that mothers^1^ are at least 18 years of age and have a baby that is less than two years old at the time of starting the P-CFT group OR they are currently pregnant and can complete the intervention prior to approximately 34 weeks gestation. Participants are excluded from the study if they are not receiving care from a P-CMHT, deemed unsuitable by the P-CMHT to receive a group intervention, assessed as acutely at risk of harm to their baby, experiencing acute psychotic symptoms, alcohol or substance misuse, active suicidality and/or lacking capacity to consent under the Mental Capacity Act 2005 (41).

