#### Recruitment and consent procedures

A member of the P-CMHT will identify potential eligible participants via case note review or in a multidisciplinary meeting. The member of the P-CMHT’s psychology team will then assess if they are suitable for the P-CFT group and if they can provide consent-to-contact regarding the study. If suitable, they will be sent a study leaflet and a copy of the participant information sheet from the lead researcher ([name]). Eligible service users have at least 24 hours to think about if they would like to take part. After 24 hours, the lead researcher will conduct a phone call with the potential participant. If the individual is happy to take part, they will be asked to provide their informed consent. All online forms will be hosted via Qualtrics (42). When providing informed consent, participants can also consent to Component 2 of this study concurrently, and opt-in to being contacted about Component 3. For Component 1, participants will complete a set of demographic questions, and six outcome measures (see **Table 1** for details). To reimburse and thank them for their time and contributions, participants can consent to being entered into a prize draw (ranging from a £25-£100 gift voucher) which will be conducted at the end of the study.

Study safety procedures will be outlined to participants as part of informed consent. Active monitoring of adverse events (AEs) will be conducted throughout the study with study participants and their clinical team. We will report any severe adverse events in a future publication reporting on outcomes.

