#### Participant inclusion/exclusion criteria

The inclusion and exclusion criteria applied to the overall study is largely consistent across Component 1 and Component 2. However, participants who are pregnant at baseline (Time 1) are excluded from Component 2, because a recording of the parent-infant dyad is required.

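### The PBQ is scheduled for participants who are still pregnant, and PBQ and CORE-10 are optional online with score retrieval stated only for baseline, so their completion rates cannot be read as acceptability

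*Protocol article*

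**What the plan says.** Four parts of the protocol article bear on this point.

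- **Who is in Component 1.** The participant inclusion/exclusion criteria admit women with a baby under two, or those for whom "they are currently pregnant and can complete the intervention prior to approximately 34 weeks gestation".
- **What is scheduled.** Table 1 marks the PBQ for Component 1 at Time 1, Time 2 and Time 3, with no restriction to postnatal participants. Table 2 gives the aim of the PBQ as "Measures difficulties in the parent-infant bond". For Component 2 the plan does act on pregnancy: "participants who are pregnant at baseline (Time 1) are excluded from Component 2, because a recording of the parent-infant dyad is required". No matching rule is given for the PBQ.
- **How PBQ and CORE-10 are collected.** Under Recruitment and consent procedures, "participants will complete a set of demographic questions, and six outcome measures". Under Secondary clinical outcomes, the PBQ and CORE-10 are described as already collected routinely by the services, and "participants are not required to complete these two measures as part of the" study's online questionnaire. If they are not completed at the baseline assessment, "the research team will request the scores from the group facilitators". Nothing is said about retrieval at Time 2 or Time 3. Table 2, as it reads here, puts the routine-collection asterisk on the CORE-10 only.
- **What the scores are for.** Under Primary feasibility and acceptability outcomes, "the rate of completion of the self-reported outcome measures across each time point will be used to signify their feasibility and acceptability". Under Data analysis of secondary outcomes, the share with clinically significant change from Time 1 to Times 2 and 3 is to be reported for every measure.

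**The concern.** A completion rate indicates acceptability only if everyone in the denominator could have completed the form and was asked to do so in the same way. For these two measures, neither condition is secured.

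A woman who is pregnant with her first child has no bond with a born infant to rate. If she leaves the PBQ blank, that says nothing about whether the questionnaire is acceptable. A participant who skips the optional PBQ or CORE-10 because her clinic has already administered it is likewise not showing that she dislikes it. The Discussion section nevertheless intends to learn from what participants skip which items and questionnaires suit this population, and the suitability of the measures is a stated objective.

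The collection rule also differs by time point as written. A missing score can be recovered at baseline, but no recovery is stated later. That can make completion appear to fall over time for reasons of procedure, and it can leave participants with a baseline score and no later score to pair with it.

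**Working it through.** **Plan's own figure.** The baseline target is half of the lower end of the stated pool: 0.50 × 64 = 32. (The stated 17 groups of at least 4 would give 68, and half of that is 34. The difference does not matter here.) I use 32 as the denominator.

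**Step 1: is there an infant to rate?** Inputs: the intervention ends by about week 34 of gestation (inclusion criteria); 8 to 12 weekly sessions (Intervention and its delivery); baseline up to 4 weeks before the first session, Time 2 up to 4 weeks after the intervention, and Time 3 six months after baseline, taken as 26 weeks (Outcomes and assessments). Birth at 40 weeks is my assumption.

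- Time 2 at the latest: 34 + 4 = week 38, so normally before birth.
- Baseline for someone finishing at week 34: from 34 − 12 − 4 = week 18 to 34 − 8 − 0 = week 26.
- Time 3 for the same person: 18 + 26 = week 44 to 26 + 26 = week 52, that is 4 to 12 weeks after birth.
- Time 3 falls before term only if baseline was before week 40 − 26 = 14.

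So at Times 1 and 2 the index infant is normally not yet born, while at Time 3 a PBQ can often be collected. For these participants a change score on the index infant cannot be formed, because there is no starting value.

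**Step 2: effect on PBQ completion.** The pregnant share is not given, so I assume 10% to 25% and that everyone with an infant completes the form.

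| Assumed share pregnant | Pregnant | With infant | Completion over all 32 | Completion over those with an infant |
|---|---|---|---|---|
| 10% | 3 (3.2) | 29 | 29/32 = 91% | 100% |
| 20% | 6 (6.4) | 26 | 26/32 = 81% | 100% |
| 25% | 8 | 24 | 24/32 = 75% | 100% |

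The shortfall at Times 1 and 2 comes entirely from the denominator.

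**Step 3: effect of optional status and baseline-only retrieval.** This applies to both PBQ and CORE-10. Assume that all 32 stay in the study, that a fraction q skip the optional online forms, that baseline is fully recovered from facilitators and counted as complete, and that nothing is retrieved later. Completion is then 100% at Time 1 and 1 − q at Times 2 and 3, with 32 × (1 − q) pairs.

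| q | Time 1 | Times 2 and 3 | Pairs of 32 |
|---|---|---|---|
| 25% | 100% | 75% | 24 |
| 50% | 100% | 50% | 16 |
| 75% | 100% | 25% | 8 |

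These values of q are illustrations. The article gives no figure for skipping.

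**Step 4: the two collection statements side by side.** The consent section has participants completing six measures, and Table 1 needs both the PBQ and the CORE-10 to reach six. The Secondary clinical outcomes section requires only four of them online. As worded, a site cannot tell whether an unanswered PBQ or CORE-10 is a missing form or a permitted omission.

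**The case against.** The best reply is that an article condenses a fuller protocol. Denominators, not-applicable codes and source flags usually sit in the full protocol or the analysis plan, and the article never says that clinic-supplied scores count as completions. The six-measure sentence may simply summarise the battery, with the later section giving the route for two of its members. Retention is the only outcome with a numerical progression threshold, per-measure completion has none, and the clinical analyses are exploratory.

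Much of this limits the point without removing it. The apparent decline in Step 3 does depend on a counting rule that the article leaves open. But the unrestricted PBQ schedule, the eligibility of pregnant women, the optional status and the baseline-only retrieval are rules the article states. Its Component 2 rule shows that the lack of an infant was recognised in one place and not carried to the other.

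A reader might infer more than the text supports:

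- **That PBQ and CORE-10 change scores are invalid.** They are not. Pregnancy does not affect the CORE-10, and anyone with both CORE-10 scores has a usable change. The same holds for the PBQ in postnatal participants with both scores.
- **That Time 1 to Time 3 bonding change is lost altogether.** It is unavailable for those with no infant at baseline and for missing pairs, not for everyone.
- **That no pregnant participant can answer the PBQ.** Some may have an older infant, and the demographic form asks the age of the youngest child.
- **That no clinic scores exist after baseline.** The article calls both measures routinely collected. It is silent on retrieving later scores, which does not show that there are none.

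**Conclusion.** The point holds in a limited form. Followed as written, the plan would produce PBQ completion rates that combine participants with no infant to rate and participants who chose not to answer. PBQ and CORE-10 completion would not be comparable with the other four measures or between time points. Some Time 1 to Time 2 or Time 3 pairs may also be lost.

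If 10–25% of 32 participants are pregnant at baseline without an older infant, about 3–8 participants are affected, and PBQ completion over all 32 cannot exceed roughly 75–90% at Times 1 and 2. That range rests on the assumed share and on all 32 forming the denominator. It does not extend to Time 3, when many will have given birth. The loss of pairs through optional completion cannot be sized from the article.

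The other four measures are unaffected, and so is the retention criterion. The point merits correction because measure completion is a primary feasibility outcome and the suitability of the measures is an objective of the study.

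**What to change.** 1. Treat the PBQ as due only at time points when the participant has a born infant to rate. Otherwise record it as not applicable and leave it out of the denominator. Compute PBQ change only for those with an infant at Time 1.
2. Use one collection rule for PBQ and CORE-10 at all three time points: either extend the facilitator request to Times 2 and 3, or include both measures in the online questionnaire at those points.
3. Record the source and date of each score, and report participant-completed and clinic-sourced completion separately. Counting only the study's own forms would not do, because it would score as non-completers those whom the plan allows to skip.
4. Reconcile the six-measure statement in the consent section, the optional status under Secondary clinical outcomes, and the Table 2 footnote.

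The cost is small: some rewording and either a little more data retrieval or, with the online route, up to 25 + 10 = 35 more items at two time points. The PBQ denominator and the reporting by source can be applied at analysis to data already collected, provided that pregnancy status and score source are known.
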